## Abstract

**Background:**

Obstructive sleep apnea (OSA) is a common disorder that affects approximately 1 billion people worldwide. Advanced age is a significant risk factor. Various treatment options have been explored to reduce the severity of OSA symptoms and physical exercise has emerged as a potential alternative therapy. Therefore, this study aims to investigate the effects of a combined exercise program with sleep education on sleep quality and on the severity of OSA in older adults.

**Methods:**

This is a randomized clinical trial with two parallel groups that will involve individuals of both genders aged between 60 and 79 years who have an apnea-hypopnea index (AHI) of more than 15 events per hour and who have not received or are currently undergoing treatment for OSA. Older adults who have engaged in regular exercise in the last six months and individuals with contraindications to exercise will be excluded. The study will assess outcomes related to OSA, including AHI, oxygen desaturation index, minimum and mean oxyhemoglobin saturation, sleep efficiency, sleep latency, and the type of respiratory events. Additionally, sleep quality-related outcomes, daytime sleepiness, physical activity, physical fitness, aerobic capacity, cognitive status, anthropometric measures, and health-related quality of life will be analyzed. Participants will be randomized to two groups: a combined exercise group (involving both resistance and aerobic training) with sleep education, and a control group that will receive only educational recommendations for managing OSA. The intervention will last 12 weeks and will consist of three sessions per week, totaling 36 exercise sessions. Sample size calculation indicates a minimum number of 36 participants.

**Discussion:**

If the hypothesis is confirmed, this clinical trial will indicate an effective non-pharmacological intervention for treating OSA in older adults. This intervention could be used as an adjunct to existing approaches designed to improve OSA management.

**Clinical trail registration:**

Brazil Clinical Trials Registry (ReBEC), identifier RBR-9hk6pgz.

## Introduction

1

Obstructive sleep apnea (OSA) is a highly prevalent breathing disorder that affects approximately 1 billion people worldwide (Benjafield et al., 2019). The prevalence of moderate to severe OSA ranges from 6 to 17% among adults and can reach up to 49% in older age groups (Senaratna et al., 2017). The main risk factors associated with OSA are obesity, male gender, craniofacial abnormalities, genetic predisposition, ethnic differences, and advanced age (Young et al., 2004; Jordan et al., 2014; Lee and Sundar, 2021).

Positive airway pressure therapy is the primary treatment for individuals with symptomatic OSA of any severity and continuous positive airway pressure (CPAP) is the gold standard among its modalities (Epstein et al., 2009; Gottlieb and Punjabi, 2020; Lee and Sundar, 2021). However, although CPAP is effective in many patients, it is not always well tolerated, a fact that can reduce patient adherence to treatment (Rotenberg et al., 2016). Additionally, CPAP can have some adverse effects (Sawyer et al., 2011), such as skin breakdown, conjunctivitis, nasal congestion, airway dryness, and gastrointestinal obstruction (Zandieh and Katz, 2010; Virk and Kotecha, 2016).

Recently, alternative treatments for OSA have been investigated and physical exercise has received notable attention from the scientific community (Peng et al., 2022). In addition to reducing the severity of the disorder by decreasing the apnea-hypopnea index (AHI) and the oxygen desaturation index (ODI), meta-analyses have highlighted the ability of exercise to improve several OSA-related outcomes, which include sleepiness, sleep quality, and sleep efficiency, as well as parameters like maximal oxygen consumption (VO_2_max), body mass index (BMI), and overall quality of life (Iftikhar et al., 2014; Aiello et al., 2016; Lins-Filho et al., 2020; Fank et al., 2022; Peng et al., 2022).

Despite these advances, the exact mechanisms underpinning the beneficial effects of exercise on symptom alleviation and OSA severity remain only partially understood (Torres-Castro et al., 2021). It is plausible that a single mechanism may not solely account for these effects; instead, a complex interplay of contributing factors could be responsible (Iftikhar et al., 2014). Notably, aerobic exercise interventions can potentially be used to manage obesity, a pivotal risk factor for developing OSA (Aiello et al., 2016). Additionally, resistance training interventions have shown the capacity to mitigate fluid accumulation in the legs, which might help prevent nocturnal fluid displacement toward the neck during sleep, thereby reducing the likelihood of upper airway collapse – an event implicated in OSA (Yumino et al., 2010; Mirrakhimov, 2013). Consequently, the combined implementation of these exercise modalities may not only promote synergistic benefits in OSA but also aligns with the health recommendations of the World Health Organization (Bull et al., 2020).

Although numerous studies have examined the impacts of exercise on OSA, adult populations have been the primary focus (Aiello et al., 2016; Lins-Filho et al., 2020; Peng et al., 2022). Thus, it is important to expand the scope of investigation by including older individuals who not only have a higher prevalence of OSA but are also more vulnerable to developing the disease (Edwards et al., 2010). It will therefore be possible to determine whether the beneficial effects of exercise observed in adults also apply to older adults.

The use of exercise as a tool for treating OSA may contribute to reducing healthcare costs. Exercise offers a low-cost option in terms of both implementation and monitoring and its cost-effectiveness has been demonstrated across different contexts (Roine et al., 2009; Garrett et al., 2011; Abu-Omar et al., 2017). Within the context of global healthcare spending, sleep disorders, including OSA, are the primary contributors (Mohit and Wickwire, 2020) and their prevalence continues to rise annually (Ensrud et al., 2020). Moreover, sleep-disordered breathing, which includes OSA, has substantial health, societal, and economic repercussions, thereby inflating healthcare expenses for both patients and society (Jennum and Kjellberg, 2011). These implications include vehicle and occupational accidents and different associated comorbidities (Knauert et al., 2015). It is therefore crucial to reduce the direct and indirect costs related to OSA, mainly through more cost-effective and noninvasive therapies (Wickwire et al., 2020).

Therefore, this study aims to investigate the effects of a combined exercise program with sleep education on sleep quality and on the severity of OSA in older adults. The results obtained will enable healthcare professionals to build their daily practice on evidence-based science, incorporating another non-pharmacological treatment option for older adults with OSA. The hypothesis is that the combination of resistance and aerobic exercises, coupled with sleep education, will be capable of reducing both the severity and symptoms of OSA in older adults when compared to the control group, which will exclusively receive educational recommendations for managing OSA.

## Methods

2

### Study design

2.1

This study is designed as a two-arm parallel group, randomized controlled trial that assesses the effects of a combined exercise program with sleep education on sleep quality and on the severity of OSA in older adults. Participants will be recruited from the waiting list for polysomnography in a city in southern Brazil. After initial screening, older people at high risk for OSA will undergo polysomnography. Older adults who meet the inclusion criteria will be randomized to the intervention or control group. The intervention will last 12 weeks, three times a week, and will be conducted at the Center for Health and Sports Sciences, State University of Santa Catarina, Brazil. The study was designed following the SPIRIT recommendations (Chan et al., 2013) and the schedule of enrolment, interventions, and assessments is shown in Figure 1.

**Figure 1 fig1:**
[figure not shown]
SPIRIT schedule of enrolment, interventions, and assessments.

### Participants

2.2

The following inclusion criteria will be applied to select the participants in this randomized clinical trial (Figure 2): age between 60 and 79 years; both genders; moderate to severe OSA with an AHI > 15 events per hour, and no history of previous or ongoing treatment for OSA. Older adults who have engaged in regular exercise in the last six months and those with contraindications (cardiovascular, respiratory, musculoskeletal, or neurological) to exercise will be excluded. Participants who do not adhere to the interventions at a rate ≥ 85% will also be excluded from the study.

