### Sample size

2.3

To determine the minimum number of participants required for the interventions, the sample size was calculated using the GPower 3.1 software. Using repeated measures ANOVA (within-subjects and between-subjects interaction) and assuming a significance level (α) of 0.05, power (β) of 0.95, and effect size of 0.35 (da Silva et al., 2022), the minimum sample size is 30 individuals. This number will be increased by 20% to account for potential sample losses, resulting in a minimum sample size of 36 participants divided into two groups: – the exercise group (EG) and the control group (CG), each consisting of 18 subjects. Losses after randomization will be included in the intention-to-treat analysis but not in the analysis of the protocol.

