### Experimental design

2.8

As previously mentioned, participants will be allocated to either EG or CG. Participants randomized to EG will undergo a 12-week intervention, three times per week, totaling 36 sessions. Each training session will last approximately 60 min and will be organized as follows: warm-up (5 min), training (50–60 min), and cool-down (5 min). Training intensities will be progressively adjusted throughout the weeks according to the principle of overload.

The intervention will consist of a training program that combines aerobic and resistance exercises within the same session. This approach is based on other studies that have applied similar training programs to adults with OSA (Kline et al., 2011; Desplan et al., 2014; Bughin et al., 2020). The combined exercise approach is also in line with the physical activity recommendations for Brazilian older adults, which suggest the prescription of both types of exercise (de Coelho-Ravagnani et al., 2021). Each training session will start with a warm-up (5 min), followed by aerobic exercise (20 min) and resistance exercises (30 to 40 min), and concluding with a cool-down (5 min).

The aerobic training protocol will be conducted on a treadmill or stationary bicycle, with intensity corresponding to the anaerobic threshold determined based on the ventilatory thresholds established in the stress test. Pre-test instructions will be provided to participants in accordance with the recommendations of the American Heart Association (Fletcher et al., 2013). Heart rate will be monitored during the sessions using a Polar heart rate monitor.

The resistance exercise protocol will consist of exercises for the legs, arms, chest, back, and abdomen. All exercises will comprise three sets, with a rest interval of 90 s. Additionally, the intervention will be divided into three phases: familiarization, load determination, and training. The familiarization phase will involve learning the proper range of motion, breathing, and rhythm for each exercise. Participants will be instructed to inhale during the eccentric phase and to exhale during the concentric phase of the exercise, performing repetitions at a tempo of two seconds for each phase of the movement.

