Loads will be determined using the maximum repetition (RM) test to define loads within the training target zone, which will be set at 10 RM in this study. This load determination is based on various studies (Jambassi Filho et al., 2011; Gurjão et al., 2012; Virtuoso et al., 2019). Participants will be instructed to perform as many repetitions as possible with a load subjectively chosen by the researcher (trial and error). During this determination process, a maximum of two attempts will be made for load definition, with a recovery interval of 3 to 5 min. If a participant completes more than 12 repetitions, 1 kg will be added for every two additional repetitions. If the number of repetitions falls below 8 RM, the load will be adjusted through trial and error. To ensure accuracy in load definition and to assess reproducibility, the tests will be repeated after a minimum interval of 48 h. Following the load determination, participants will start the resistance exercises as part of the intervention.

In addition to the exercise, participants in EG will also receive sleep education, which will include information on sleep hygiene and on the pathophysiology, risk factors, and treatments of OSA. Sleep education will also be administered to participants randomized to CG so that they would adhere to the recommendations of the American Academy of Sleep Medicine (AASM) (Epstein et al., 2009). A booklet containing information about sleep hygiene will be provided to CG participants before the start of the intervention. Furthermore, recorded videos on the pathophysiology, risk factors, and treatments for OSA will be sent remotely to the participants. These materials will be systematically distributed over the 12-week period. The participants will also be asked to maintain their normal activities and not to perform exercise. After the research period, CG participants will be referred for appropriate treatment according to medical recommendation.

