### Data analysis

2.10

The data will be organized using Microsoft Excel and subjected to statistical analysis using the IBM SPSS 20.0 software. Descriptive statistics will be employed to assess all variables and will include absolute frequency, relative frequency, mean, and standard deviation. Data distribution normality will be tested by the Shapiro–Wilk test. Baseline characteristics will be examined based on the nature of the variables (numerical or categorical). Differences between groups at baseline will be evaluated using one-way analysis of variance (ANOVA) or the Kruskal-Wallis test for numerical variables and Pearson’s chi-square or Fisher’s exact test for categorical variables.

Repeated-measures ANOVA will be applied to assess post-intervention group-by-time interactions. Multiple comparisons will be performed using Tukey’s post-hoc test. Furthermore, potential associations between deltas (Δ) – mean changes before and after the intervention – of OSA-related outcomes (AHI and ODI) and possible explanatory variables (VO_2_, BMI, and NC) will be explored using Pearson’s or Spearman’s correlation test, depending on data normality. A 95% confidence interval will be employed in all analyses, corresponding to a significance level of 0.05 (5%). As highlighted previously, losses after randomization will be included in the intention-to-treat analysis but not in the analysis of the protocol. (Supplementary Table S1) shows the summary of the outcomes along with their respective measurement tool.

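### The 85% adherence exclusion acts after randomisation and, read literally, conflicts with the promised intention-to-treat analysis

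*Protocol article*

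**What the plan says.** Section 2.2 (Participants), after the inclusion and exclusion criteria, adds: "Participants who do not adhere to the interventions at a rate ≥ 85% will also be excluded from the study".

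Section 2.1 (Study design) places randomisation after eligibility has been established: "Older adults who meet the inclusion criteria will be randomized to the intervention or control group".

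On participants lost later, section 2.3 (Sample size) says: "Losses after randomization will be included in the intention-to-treat analysis but not in the analysis of the protocol". Section 2.10 (Data analysis) repeats this almost word for word. Neither section mentions adherence or 85%.

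Section 2.8 (Experimental design) describes what each arm has to adhere to. For the exercise group: "Participants randomized to EG will undergo a 12-week intervention, three times per week, totaling 36 sessions". For the control group: "A booklet containing information about sleep hygiene will be provided to CG participants before the start of the intervention", and "recorded videos on the pathophysiology, risk factors, and treatments for OSA will be sent remotely to the participants". Controls are also asked to keep to their usual activities and not to exercise. The article states no measure of control-arm adherence.

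**The concern.** An eligibility criterion should be decidable before allocation. Adherence to a 12-week programme is not, so the rule removes people who have already been randomised. An intention-to-treat analysis keeps exactly those people. A team that follows 2.2 as written could stop following non-adherers and never post-test them, and no later analysis could recover outcomes that were not collected.

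The rule is also unlikely to fall evenly on the two arms. One arm has sessions that can be counted and missed, and the other receives a booklet and videos. If low attenders would have changed differently from high attenders, removing them from one arm compares a selected group with an unselected one. Their removal would also hide how many older adults with OSA can complete the programme.

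**Working it through.** **1. Passages side by side.** Section 2.2 removes low adherers from the study and names no analysis set. Sections 2.3 and 2.10 keep post-randomisation losses in one analysis and leave them out of the other. The article has no sentence linking the two rules. A randomised participant with low attendance is out under the first and, if counted as a loss, in under the second.

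**2. The threshold.** 0.85 × 36 = 30.6 sessions. Attending 31 gives 31/36 = 86.1% and the participant stays. Attending 30 gives 30/36 = 83.3% and the participant is excluded. Missing six sessions in 12 weeks is enough.

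**3. How many might be excluded.** The documents give no expected attendance. If each session is attended independently with probability p (an assumption), the share with 30 or fewer of 36 is binomial:

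| p | Share excluded | Of 18 exercisers |
|---|---|---|
| 0.95 | 0.8% | 0.1 |
| 0.90 | 14.5% | 2.6 |
| 0.85 | 45.9% | 8.3 |
| 0.80 | 75.4% | 13.6 |

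Removing 4 or 5 of 18 (22% or 28%) therefore corresponds to average attendance between 85% and 90%.

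**4. The plan's own sample size, and power.** Inputs from 2.3: "assuming a significance level (α) of 0.05, power (β) of 0.95, and effect size of 0.35", for the group-by-time interaction. The correlation between repeated measures is not given; I assume ρ = 0.5, with k = 2 groups and m = 2 time points.

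- λ = f²·N·m/(1−ρ) = 0.1225 × 30 × 2/0.5 = 14.7 on 1 and 28 df gives power 0.959. N = 28 gives 0.946, so the stated 30 reproduces.
- 30 × 1.2 = 36, as stated. At 18 v 18 the power is 0.983.
- With four exercisers removed, the standardised difference in change is 2f·√(2/(1−ρ)) = 0.7 × 2 = 1.4, so λ = 1.96 × 14 × 18/32 = 15.4 and power is 0.967.

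Loss of power is therefore not the issue.

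**5. Bias under no true effect.** Let r be the correlation between adherence and change in outcome, positive when better attenders improve more for reasons unrelated to exercise. Remove the lowest-adherence exercisers and leave the controls intact. The bias equals r times the mean standardised adherence of those kept. For the top 14 of 18 that mean is 0.363, and for the top 13 of 18 it is 0.442. The bias is then 0.363 × 0.3 = 0.109 and 0.363 × 0.5 = 0.182 with four removed, and 0.442 × 0.3 = 0.133 and 0.442 × 0.5 = 0.221 with five removed. Rejection rates for a two-sided 5% t test on change scores come from 200,000 simulated trials per row:

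| Removed | r | Bias (SD of change) | Rejection rate |
|---|---|---|---|
| 4 | 0 | 0.00 | 5.0% |
| 4 | 0.1 | 0.04 | 5.1% |
| 4 | 0.3 | 0.11 | 6.1% |
| 4 | 0.5 | 0.18 | 8.3% |
| 5 | 0 | 0.00 | 5.0% |
| 5 | 0.1 | 0.05 | 5.1% |
| 5 | 0.3 | 0.13 | 6.6% |
| 5 | 0.5 | 0.22 | 9.5% |

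Neither the number removed nor r can be taken from the documents.

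**The case against.** The strongest reply is that the rules can coexist. Someone excluded for low adherence could be treated as a loss after randomisation, kept in the intention-to-treat analysis and dropped only from the per-protocol one. Sections 2.3 and 2.10 are the only places that say how losses are analysed, and they favour intention to treat. On that reading, 2.2 holds one misplaced sentence that sets the per-protocol threshold. This stands as a possible intention, and it means a reader should not infer that the sponsor plans to analyse adherers only. It does not remove the defect, because the text says neither that non-adherers are retained losses nor that 85% is confined to the per-protocol set.

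A second reply is that 2.2 speaks of interventions in the plural and that controls receive materials over the 12 weeks and an instruction not to exercise, either of which could be monitored. That is fair. A reader might infer that the rule applies to the exercise arm alone, but the documents do not say so. They support only the weaker statement that one arm has countable sessions and the other has no stated measure. The article is condensed, and a control-arm measure may exist elsewhere.

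Third, the direction of the bias is not given. It favours exercise only if better attenders would have done better anyway, and nothing in the article describes who would attend poorly. This also stands.

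**Conclusion.** The point holds as an unreconciled contradiction with a conditional bias. Section 2.2, followed literally, is a post-randomisation exclusion that conflicts with the intention-to-treat statements in 2.3 and 2.10.

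With 4 to 5 of 18 exercisers removed, none of the controls removed, and a correlation of 0.3 to 0.5, the spurious difference is about 0.11 to 0.22 SD of change and the type I error about 6% to 9.5% instead of 5%. At a correlation of 0.1 the effect is negligible, and at zero there is essentially none. The probable direction is towards exercise, which is the trial's hypothesis, but that is a judgement and cannot be derived from the article.

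A reader might go further and conclude that the randomised comparison is destroyed. The figures do not support that: the inflation is modest over this range, and it arises only if the excluded participants are actually left out of the main analysis. The matter still needs correcting before the data are analysed, and preferably before participants are lost to follow-up, because unmeasured outcomes cannot be restored.

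**What to change.** Delete the adherence sentence from 2.2. State in 2.10 that every randomised participant is followed up, post-tested where possible, and analysed in the assigned arm whatever the attendance, and that this is the main analysis. Use the 85% threshold (at least 31 of 36 sessions in the exercise arm) only to define the secondary per-protocol set, and say there what adherence means for the control arm, if it applies to that arm.

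The sample size does not change. The cost in text is a few sentences. The practical cost is the effort of bringing poor attenders back for post-tests; whether these visits are already scheduled cannot be confirmed, because the schedule figures are not shown. The effect estimate may be somewhat smaller than one based on adherers alone.
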